### Sample size

The sample size is driven by the VIBRA trial [22]. We assume that to achieve the VIBRA trial [22] sample size (minimum 262 HIV-positive individuals not on ART) by testing about 10,000 individuals in 100 villages, based on a previous trial [32]. According to a previous home-based HIV-testing campaign [33], we estimate an HIV-testing coverage rate of individuals aged 12 years or older in rural villages of 63%. We consider a 15% increase in coverage as relevant from a policy perspective. Using an intra-cluster correlation (ICC) of 0.028, with a sample of 100 clusters, we will require a sample size of 450 in order to have > 90% power to detect an increase in coverage rates to 78% or higher. This corresponds to an increase of 1.17 (variance inflation factor (VIF)) from the 386 individuals required in the absence of clustering. If we vary the ICC for villages and include an additional ICC for clustering at the household level [34], the maximum VIF would be 8.3 corresponding to a maximum sample size of 3204 needed to ensure 90% power to detect a 15% difference, well below the expected 10,000 individuals to be included. Table 3 displays the sample size calculations considering all relevant factors under different scenarios.

**Table 3 Tab3:** Sample size estimations for the HOme-based SElftestiNG (HOSENG) trial

Average village size	Average household size	ICC (village)	ICC (household)	VIF	Total number of clusters	Total sample size
30	2	0.028	0.05	1.04	100	402
30	2	0.028	0.1	1.07	100	413
30	2	0.05	0.05	1.20	100	462
30	2	0.05	0.1	1.34	100	518
30	2	0.1	0.05	2.95	100	1139
30	2	0.1	0.1	4.4	100	1699
30	4	0.028	0.01	1.06	100	410
30	4	0.028	0.05	1.31	100	507
30	4	0.028	0.1	1.62	100	628
30	4	0.028	0.5	4.12	100	1592
30	4	0.05	0.01	1.09	100	420
30	4	0.05	0.05	1.44	100	556
30	4	0.05	0.1	1.88	100	726
30	4	0.05	0.5	5.4	100	2085
30	4	0.1	0.01	1.15	100	442
30	4	0.1	0.05	1.73	100	668
30	4	0.1	0.1	2.46	100	950
30	4	0.1	0.5	8.3	100	3204

*ICC* intracluster correlation coefficient, *VIF* variance inflation factor

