Baseline characteristics will be presented according to randomized groups; no formal testing will be performed. Categorical variables will be described with absolute and relative frequencies and continuous variables with medians and interquartile ranges. As with the primary analysis, secondary endpoints will be analyzed with multi-level logistic regression models including village and household as random effects. All results will be presented as odds ratios and 95% confidence intervals. The potential effect modification of sociodemographic determinants (age groups, gender, education status, employment status, HIV-testing history) on all endpoints will be assessed by including interaction terms in the models. If the Wald test results for the interaction terms are significant, intervention effects will be presented separately by the levels of these factors. Sensitivity analyses will be conducted in order to provide evidence that the result seen from the primary analysis are robust. In order to assess the reliability of the model fit, we will perform a quadrature check. In case of unreliable model fit, we will use generalized estimating equations to fit our model which will provide population-averaged odds ratios and 95% confidence intervals. However, this model would not allow inclusion of more than one random effect although including the highest level of clustering is suggested to be sufficient [38]. All analyses will be done using Stata (version 14, Stata Corporation, Austin, TX, USA). For all tests, we will use two-sided *p* values with an alpha = 0.05 level of significance.

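### The sample-size figures contradict one another: five Table 3 rows are mislabelled, the village ICC is used in two incompatible ways, and the headline VIF of 1.17 fits no stated design

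*Protocol article*

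**What the plan says.** All figures are in the protocol article, Sample size section and Table 3. Enrolment is set by the linked VIBRA trial, whose target is to be met "by testing about 10,000 individuals in 100 villages". For HOSENG, control coverage is taken as 63%, and the aim is "to have > 90% power to detect an increase in coverage rates to 78% or higher". With a village ICC of 0.028 and 100 clusters the required total is 450. The text adds: "This corresponds to an increase of 1.17 (variance inflation factor (VIF)) from the 386 individuals required in the absence of clustering".

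The village ICC is then varied and a household-level ICC is included as well, giving the statement that "the maximum VIF would be 8.3 corresponding to a maximum sample size of 3204 needed to ensure 90% power to detect a 15% difference". This is judged well below 10,000. The text says that "Table 3 displays the sample size calculations considering all relevant factors under different scenarios". The table's ICC columns are headed simply as village and household, with no further definition. The Analyses section sets the test: "we will use two-sided *p* values with an alpha = 0.05 level of significance".

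**The concern.** Three features of the printed numbers cannot all be right.

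- At the same two ICCs, larger households should not reduce the VIF. Yet Table 3 prints 2.95 for households of 2 and 1.73 for households of 4 at ICCs 0.1/0.05 (village/household), and 4.4 against 2.46 at 0.1/0.1.
- A further level of clustering should not reduce the VIF. Yet village clustering at 0.028 is given as 1.17 in the text, and the table gives 1.06 once a household ICC of 0.01 is added.
- A VIF of 1.17 at ICC 0.028 should correspond to the number of people per village in the design it describes.

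This section is the article's power justification for HOSENG, and Table 3 could be reused by others planning village-and-household trials without 10,000 people in reserve.

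**Working it through.** **Inputs (Sample size; Analyses).** 63% versus 78%, two-sided 0.05, 90% power, equal arms, 100 clusters, village ICC (ICCv) 0.028 to 0.1, household ICC (ICCh) 0.01 to 0.5, household size h of 2 or 4, and about 10,000/100 = 100 people per village. The table's village size of 30 is read as households. This is an inference, but village size is classed in households under Cluster sampling and randomization, and reading 30 as individuals does not reproduce the table.

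**Unclustered size.** The usual two-proportion formula gives 192.2, so 193 per arm and 386 in total. This reproduces.

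**Household-size-4 rows.** All 12 reproduce within one person as

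VIF = 1 + (h−1)·ICCh + h·29·ICCv·ICCh, N = 386·VIF.

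For the maximum: 1 + 3·0.5 + 116·0.1·0.5 = 8.30, and 386·8.30 = 3,204. For 0.028/0.01: 1 + 0.03 + 116·0.028·0.01 = 1.062, N = 410. The two ICCs are multiplied together.

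**Household-size-2 rows.** The same formula was applied to the printed labels, and the ICC pairs that recover each printed N were found:

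| Printed ICCv/ICCh | Printed N | Formula N at printed label | Pair that recovers printed N |
|---|---|---|---|
| 0.028/0.05 | 402 | 437 | 0.05/0.01 |
| 0.028/0.1 | 413 | 487 | 0.1/0.01 |
| 0.05/0.05 | 462 | 461 | 0.05/0.05 |
| 0.05/0.1 | 518 | 537 | 0.1/0.05 |
| 0.1/0.05 | 1139 | 517 | 0.05/0.5 |
| 0.1/0.1 | 1699 | 648 | 0.1/0.5 |

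All six sizes are recovered within one person, but only one label is correct.

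**Ordinary village ICC.** If ICCv is the correlation between two people of one village in different households, and ICCh that between two people of one household, then with m people per village

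VIF = 1 + (h−1)·ICCh + (m−h)·ICCv.

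Worst scenario (h = 4, 0.1/0.5):

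- m = 120 (30 households of 4): 1 + 1.5 + 11.6 = 14.1.
- m = 100: 1 + 1.5 + 9.6 = 12.1.

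**Headline VIF.** 450/386 = 1.17. With ICC 0.028:

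- 450/100 = 4.5 per village: 1 + 3.5·0.028 = 1.098, and 386·1.098 = 424.
- 100 per village: 1 + 99·0.028 = 3.77.
- A VIF of 1.17 needs 1 + 0.17/0.028 = 7.1 people per village, which is neither.

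A continuity-corrected base of 412 times 1.098 gives 452, so 450 and 386 may come from different methods. That origin is conjecture; the mismatch is not.

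**Planned design, 100 villages of 100 people.**

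| VIF | Effective n = 10,000/VIF | Power, 63% v 78% | Difference detectable with 90% power |
|---|---|---|---|
| 3.77 | 2,651 | > 99.9% | 6.0 points |
| 12.1 | 826 | 99.7% | 10.5 points |

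**The case against.** **The product may be legitimate.** If the village ICC means the correlation of household means within a village, then ICCv·ICCh is exactly the individual-level village correlation and the table's formula is right. Four household-size-4 rows (0.028/0.01, 0.05/0.01, 0.1/0.01, 0.1/0.05) support that reading. Under an ordinary village ICC, household members share the village too, so a household ICC below the village ICC is impossible. This stands as a possible defence. But the article never gives that definition, uses the same 0.028 as an ordinary village ICC in the headline, and presents the household ICC as an addition.

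**A reader might infer that the required sizes are badly understated**, for example that 386·14.1 = 5,443 people are needed rather than 3,204, or 386·4.28 = 1,651 rather than 410. The document does not support this. Every row fixes 100 clusters, and 5,443 people over 100 villages is 54 per village, where the VIF is about 7.5. Solved with 100 clusters, N = 386·(1 + 1.5 + (N/100 − 4)·0.1) gives about 1,320, and the 0.028/0.01 row gives about 397. Both are below the printed sizes. An 11-fold understatement of the VIF (12.63 against 1.15) is equally tempting, but it comes from the 0.1/0.01 row, one of the impossible combinations under the formula that produces it.

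**The headline claim itself holds.** The article does not say that 1.17 applies at 100 people per village, and 450 people at 4.5 per village do give about 92% power.

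**Nothing decided depends on the table.** VIBRA drives enrolment. That is correct and limits the weight of the point, but not the need to correct printed numbers.

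**Conclusion.** The point holds as an error of calculation and reporting. Five of six household-size-2 rows are mislabelled; this rests only on the formula that reproduces the other rows and on the two reversals visible in print. The text and the table use 0.028 in incompatible senses. On the sense used in the text, 8.3 is not the maximum VIF: the same scenario gives 14.1 at 120 people per village or 12.1 at 100. The 1.17 matches neither 4.5 people per village (1.10) nor 100 (3.77).

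A reader might conclude that the trial is underpowered. It is not: power for a 15-point difference is above 99% across VIFs of 3.8 to 12.1. If the household ICC is instead an extra component on top of the village ICC, the worst VIF at 100 people per village is 1 + 3·0.6 + 96·0.1 = 12.4, and power is still 99.7%. The figure of 386 and the judgement that 10,000 people is enough both stand. The results assume villages of equal size, 25 households of 4 in the worst case, and the article's own range of ICCs.

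**What to change.** 1. Correct the ICC labels of the five household-size-2 rows.
2. Either recompute Table 3 with VIF = 1 + (h−1)·ICCh + (m−h)·ICCv, keeping only scenarios where the household ICC is at least the village ICC, or state that the village ICC is the correlation of household means and stop using 0.028 as an individual-level ICC in the text.
3. Replace the 450 / 1.17 and 8.3 / 3204 statements with the VIF, power and detectable difference for about 100 villages of 100 people: VIF about 3.8 to 12.1, power above 99% for 63% versus 78%, and about 6.0 to 10.5 points detectable with 90% power. If required sizes are kept, solve them with the number of clusters fixed at 100.

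The cost is a correction to one table and a few sentences. No clusters or participants are added, and the analysis is unchanged.

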### Analyses

Analyses will be reported following Consolidated Standards of Reporting Trials (CONSORT) guidelines for cluster-randomized trials [35]. Clusters will be set as the unit of randomization (stratified by district, size of village, and village access to the nearest health facility), whereas individuals are set as the unit of analysis. An intention-to-treat set will be used, i.e., all study participants will be evaluated according to arm assignment at randomization. The primary analysis will use multi-level logistic regression models including village and household as random effects to assess the difference between HIV-testing coverage in the intervention versus the control arm. These models will be adjusted for the pre-specified randomization stratification factors and relevant baseline factors (age groups, gender, education status, employment status, HIV-testing history) that may be randomly unbalanced between intervention and control clusters [36, 37].

Baseline characteristics will be presented according to randomized groups; no formal testing will be performed. Categorical variables will be described with absolute and relative frequencies and continuous variables with medians and interquartile ranges. As with the primary analysis, secondary endpoints will be analyzed with multi-level logistic regression models including village and household as random effects. All results will be presented as odds ratios and 95% confidence intervals. The potential effect modification of sociodemographic determinants (age groups, gender, education status, employment status, HIV-testing history) on all endpoints will be assessed by including interaction terms in the models. If the Wald test results for the interaction terms are significant, intervention effects will be presented separately by the levels of these factors. Sensitivity analyses will be conducted in order to provide evidence that the result seen from the primary analysis are robust. In order to assess the reliability of the model fit, we will perform a quadrature check. In case of unreliable model fit, we will use generalized estimating equations to fit our model which will provide population-averaged odds ratios and 95% confidence intervals. However, this model would not allow inclusion of more than one random effect although including the highest level of clustering is suggested to be sufficient [38]. All analyses will be done using Stata (version 14, Stata Corporation, Austin, TX, USA). For all tests, we will use two-sided *p* values with an alpha = 0.05 level of significance.

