### Design

The HOSENG trial is a cluster-randomized controlled, superiority trial in a resource-limited setting. The rationale for a cluster-randomized design at village level is (1) the reliance of the trial on the village health workers (VHWs) and (2) the high risk of cross-contamination between the study arms if randomization would be done at the individual or household level. The HOSENG trial, with its home-based HIV-testing campaign, provides a recruitment platform for another trial, the VIBRA (Village-Based Refill of ART) trial [22], and thus they are based on the same cluster-randomization and run in parallel. Together, HOSENG and VIBRA [22] constitute the GET ON (GETting tOwards Ninety) research project. To ensure a balance in the exposure to the HOSENG intervention in the two arms, the clusters (villages) will be randomized into four potential groups in a 1:1:1:1 allocation.

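### The HOSENG analysis omits the VIBRA allocation, so it does not show whether the HOSENG effect holds with and without the co-randomized intervention

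*Protocol article*

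**What the plan says.** The Design section of the protocol article says of HOSENG and VIBRA that "they are based on the same cluster-randomization and run in parallel", and that "the clusters (villages) will be randomized into four potential groups in a 1:1:1:1 allocation". The reason it gives is to balance exposure to HOSENG between arms. The section on cluster sampling and randomization adds that blocks of 4 were used within strata of district, village size and access.

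The Analyses section specifies a multi-level logistic model with village and household random effects. On covariates it says "These models will be adjusted for the pre-specified randomization stratification factors and relevant baseline factors". The baseline factors named are age group, gender, education, employment and testing history, and the same five are the only effect modifiers named. Sensitivity analyses are promised but not described.

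The article nowhere states a VIBRA term, results by VIBRA arm, or an assumption that the two interventions do not interact. Fig. 1 is not shown, so reading the four groups as HOSENG by VIBRA is an inference from the Design section.

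**The concern.** The explicit covariate and effect-modifier lists cover characteristics that were not randomized and leave out the one other factor that was. The two interventions run in the same villages at the same time.

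There is a plausible route by which one could affect the other. Self-test kits are followed up and collected by village health workers, control villages refer absent or declining people to the same workers or to the health facility, and the endpoint stays open for 120 days. The Discussion itself flags the extra workload for village health workers.

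The Discussion also aims the result at policy in Lesotho and similar countries, where VIBRA may not be in place. If the HOSENG effect differed with and without VIBRA, a single pooled odds ratio would describe a mixture of two settings and would not reveal it.

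**Working it through.** **The plan's own figures.** The Sample size section assumes 63% coverage in control and says "Using an intra-cluster correlation (ICC) of 0.028, with a sample of 100 clusters" the trial needs 450 people "in order to have > 90% power to detect an increase in coverage rates to 78% or higher". A two-sided 5% comparison of 63% with 78% at 90% power needs 193 per arm, or 386, which matches the unclustered figure exactly. For the clustered figure, 450/386 = 1.17, the stated inflation factor. With a continuity correction (206 per arm) and 50 villages per arm, 2 × 206 × 50 × 0.972 / (50 − 206 × 0.028) = 453, within 3% of 450. Adding a VIBRA term does not change the required sample size.

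**Inputs for the check.** Coverage 63% and 78%; village ICC 0.028, with 0.05 and 0.1 from Table 3; about 10,000 people in 100 villages, so m = 100 per village (assumed equal); four equal groups, so 25 villages each. VIBRA effects on coverage of 0 to 10 points are assumptions. Household clustering is not added. The check is on the coverage scale, not the odds-ratio scale.

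**Variance of a village proportion at ICC 0.028.** p(1 − p)[1 + (m − 1)ICC]/m, with 1 + 99 × 0.028 = 3.772:
- control: 0.63 × 0.37 × 3.772/100 = 0.00879
- intervention: 0.78 × 0.22 × 3.772/100 = 0.00647
- mean: 0.00763

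**Cost in precision of leaving VIBRA out.** A balanced factor with effect e adds e²/4 to the village variance.

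| Assumed VIBRA effect | e²/4 | SE ratio without/with term, ICC 0.028 | SE ratio, ICC 0.1 |
|---|---|---|---|
| 0 points | 0 | 1.000 | 1.000 |
| 2 points | 0.0001 | 1.007 | 1.002 |
| 5 points | 0.000625 | 1.040 | 1.014 |
| 10 points | 0.0025 | 1.152 | 1.055 |

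At ICC 0.028 the SE with the term is therefore about 0.7%, 4% and 13% smaller for 2, 5 and 10 points.

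**Simulation.** Village proportions were drawn from a beta-binomial distribution at ICC 0.028 with 25 villages per group, 4,000 runs per scenario. The estimated HOSENG difference was identical with and without the VIBRA term. Its mean SE went from 1.756 to 1.744 points for a 2-point VIBRA effect, from 1.81 to 1.74 for 5 points, and did not change for zero. When the true HOSENG effect was set to 10 points in one VIBRA arm and 20 in the other, the pooled estimate averaged 15.0 points and gave no sign of the difference.

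**What results by VIBRA arm could show.** With 25 villages per group, the SE of the HOSENG effect within one VIBRA arm is √[(0.00879 + 0.00647)/25] = 2.5 points at ICC 0.028. It is 3.1 at ICC 0.05 and 4.2 at ICC 0.1. The 95% half-widths run from 1.96 × 2.5 ≈ 5 to 1.96 × 4.2 ≈ 8 points, which is informative against a 15-point target.

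**Interaction test.** Its SE is √2 times the within-arm SE: 3.5, 4.4 and 5.9 points. The difference detectable with 80% power is (1.96 + 0.84) × SE, or about 9.8, 12.3 and 16.6 points.

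**The case against.** The strongest counter-case has four parts.

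- **Nothing in the article suggests a sizeable VIBRA effect on testing.** VIBRA enrolment is assessed after a confirmed positive test, and its minimum sample is 262 people against about 10,000 tested, or 2.6%. This stands. It is why precision cannot lead the point.
- **A reader might infer that the model gives up useful precision.** At ICC 0.028 the between-village variance is 0.028 × 0.63 × 0.37 = 0.0065, so an omitted effect of 5 or 10 points adds about 10% or 38% to it. The documents do not support that reading. The effects are assumed, and those percentages are not the loss in the treatment estimate, whose SE changes by about 4% or 13%, and by under 1% for 2 points. Power at about 10,000 people is above 99.8% across ICCs of 0.028 to 0.1 even without the term.
- **There is no bias and no broken rule.** VIBRA is not a stratification factor, so adjustment for those factors is complete as stated, and blocked allocation protects the estimate. This also stands. Balance is only approximate, since 103 released villages do not divide evenly by four, but that is not material.
- **A condensed article may leave this to an analysis plan.** This stands in part. The sensitivity analyses are unnamed and an analysis plan was not available, so one cannot conclude that a check by VIBRA arm is ruled out. But the article does fix its adjustment and effect-modifier lists, and both leave out the other randomized factor.

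**Conclusion.** The point holds as a modest one about consistency. The stated analysis does not show whether the HOSENG effect is similar in villages with and without VIBRA, although the randomization makes that comparison available. It does not hold as a claim of bias or of meaningful lost power: the HOSENG estimate is essentially unaffected, and the precision gain runs from nil to about 13% of the SE depending on an unknown VIBRA effect, with the documents pointing to the low end.

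This rests on reading the four groups as HOSENG by VIBRA, on 25 villages per group with 100 people each, and on calculations on the coverage scale without household clustering.

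**What to change.** - Add VIBRA allocation as a fixed effect in the primary 120-day coverage model and in the all-ages 120-day coverage model. It is not needed for blood-based uptake, which is measured on the campaign day, or for self-test uptake, which arises only in HOSENG intervention villages.
- State that the pooled odds ratio assumes no HOSENG-by-VIBRA interaction.
- Pre-specify, as a supportive analysis, the HOSENG effect with its 95% CI within each VIBRA arm.
- If an interaction test is reported, describe it as low-powered (80% power only for differences of about 10 to 17 points), so that a non-significant result is not read as proof of consistency.

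The cost is one model term, one sentence and a short table. Village assignment is already loaded in the study database, and the sample size does not change.

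### The design target is an absolute gain in coverage, but every result is fixed as an odds ratio, and the fallback model changes which odds ratio is reported

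*Protocol article*

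**What the plan says.** The Sample size section sets the effect of interest on the coverage scale: "We consider a 15% increase in coverage as relevant from a policy perspective". The calculation is made "in order to have > 90% power to detect an increase in coverage rates to 78% or higher" from an assumed 63%. The Endpoints section defines the primary endpoint as a proportion of people aged 12 or older, and the Eligibility criteria section describes coverage as an outcome of the whole surveyed population.

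According to the Analyses section, a multi-level logistic model with village and household random effects, adjusted for stratification factors and individual baseline factors, is used "to assess the difference between HIV-testing coverage in the intervention versus the control arm". The same section then fixes the effect measure: "All results will be presented as odds ratios and 95% confidence intervals". If a quadrature check shows unreliable fit, "we will use generalized estimating equations to fit our model which will provide population-averaged odds ratios and 95% confidence intervals". The article names no risk difference, risk ratio or standardised coverage.

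**The concern.** The size of benefit that the investigators call relevant is stated in percentage points of population coverage, but the planned effect estimate and its interval are on the odds scale. Two consequences follow.

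First, an odds ratio does not map to a fixed number of points. The gain that it implies depends on control coverage and, for the mixed-model odds ratio, also on the amount of clustering. A reader who wants the absolute gain with an interval that respects village and household clustering will not find one in the planned output.

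Second, the mixed-model odds ratio compares people at the same values of the village and household effects, whereas the GEE odds ratio averages over clusters. With a common outcome and appreciable clustering the two differ even when both models are correct. Under the plan as written, a numerical diagnostic can therefore change the quantity being estimated as well as the estimation method.

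**Working it through.** **1. Confirm the design scale.** Inputs from Sample size and Analyses: p1 = 0.63, p2 = 0.78, two-sided alpha 0.05, 90% power. I take the HOSENG comparison as 1:1. With the pooled two-proportion formula and no continuity correction:

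n per arm = [1.960 × √(2 × 0.705 × 0.295) + 1.282 × √(0.63 × 0.37 + 0.78 × 0.22)]² / 0.15² = [1.264 + 0.815]² / 0.0225 ≈ 192.2, rounded up to 193.

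The total is 386, which matches the plan's own figure ("from the 386 individuals required in the absence of clustering"). A relative 15% increase would be 0.63 × 1.15 = 0.7245 and would need 1,026 in total. The target is therefore 15 percentage points.

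**2. Population-averaged odds ratio at the target.** (0.78/0.22) / (0.63/0.37) = 3.545 / 1.703 = 2.08.

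**3. Conditional odds ratio for the same two coverages.** Take logit P = b + u with u normal, mean 0, and variance ICC/(1 − ICC) × π²/3. Solve for b in each arm so that coverage averaged over u is exactly 63% and 78%; the conditional odds ratio is exp(b₂ − b₁). Covariates are left out. Treating Table 3's ICCs as latent-scale is an assumption, because the article does not say which scale they are on.

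| Total latent ICC | Variance of u | Conditional OR | Excess over 2.08 |
|---|---|---|---|
| 0.028 | 0.095 | 2.11 | 1% |
| 0.10 | 0.366 | 2.19 | 5% |
| 0.20 | 0.822 | 2.33 | 12% |
| 0.50 | 3.290 | 3.02 | 45% |

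If the ICCs are instead on the observed scale, the conditional odds ratios are 2.12 at 0.028, 2.24 at 0.10 and 4.18 at 0.50.

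**4. Where these ICCs sit in the plan.** The base case is a village ICC of 0.028. A household ICC of 0.5 appears in 3 of the 18 rows of Table 3. In the other 15 rows the village and household ICCs sum to at most 0.1 + 0.1 = 0.20.

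**5. The reverse reading.** Suppose the mixed model reports a conditional odds ratio of 2.08 and control coverage is 63%. Coverage in the intervention arm is then 77.8% at a latent ICC of 0.028, 77.1% at 0.10, 76.3% at 0.20 and 73.4% at 0.50. The gains are 14.8, 14.1, 13.3 and 10.4 points.

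**6. Dependence on control coverage, whatever the ICC.** With control odds o = p/(1 − p), a population-averaged odds ratio of 2.08 gives coverage 2.08·o / (1 + 2.08·o):

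- control 63%: 78.0%, a gain of 15.0 points
- control 70%: 82.9%, a gain of 12.9 points
- control 80%: 89.3%, a gain of 9.3 points

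**7. Would an absolute interval be informative?** Assume the expected 10,000 people split equally. The half-width is 1.96 × √[VIF × (0.2331 + 0.1716)/5,000], where VIF is the variance inflation factor. That gives 1.9 points at the plan's VIF of 1.17 and 5.1 points at its maximum of 8.3, so under these assumptions the interval is narrow relative to a 15-point gain.

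**The case against.** The strongest reply is that little is lost. The endpoint is itself a proportion, and nothing in the article withholds coverage by arm. The sentence fixing odds ratios follows the description of the regression models and most naturally governs how model effects are expressed. Odds ratios from mixed logistic models are a standard measure for a binary endpoint in a cluster trial. The fallback is specified in advance and labelled as population-averaged. Standardisation could be left to a statistical analysis plan that is not shown.

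Much of this stands, and it rules out four stronger readings that a reader might infer:

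- *The policy question goes unanswered, or nobody could tell whether coverage rose by 15 points.* Crude coverage by arm can be shown, so this does not follow.
- *Fifteen points is a success threshold.* It is the design difference of a superiority trial. No rule requires the estimate to reach it, and the planned test is unaffected.
- *The cost-effectiveness analysis cannot be done.* The section on additional research promises costs per participant reaching the endpoint in each arm and per additional confirmed result. Both need arm-level counts, which points to absolute outcomes being available.
- *The headline can move by almost half according to which model converges.* A shift of that size needs the household ICC of 0.5. The trigger is a check on reliability of fit, and if it fails the mixed-model figure is not a credible competitor.

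Two things survive. Crude percentages carry no cluster-adjusted interval for their difference. And the article does more than stay silent: it fixes the odds ratio for all results and fixes the change of model, so an analysis plan adding a common absolute measure would have to depart from the article's wording.

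**Conclusion.** The point holds in a limited form. The trial is designed around an absolute gain in population coverage, yet the only effect measure that it commits to is an odds ratio, and that odds ratio changes meaning if the quadrature check fails. The change of meaning is negligible at the base-case village ICC (2.11 against 2.08) and at most about 12% in 15 of the 18 scenarios of Table 3. It is large (3.02 against 2.08) only with the upper household ICC. These sizes assume latent-scale ICCs that add across levels, normal random effects and no covariates. The dependence on control coverage (15.0 points at 63%, 9.3 at 80%) needs none of those assumptions. The sample size and the validity of the superiority test are not in question. What is affected is how directly the result speaks to the stated target, and whether the estimand stays the same under both models.

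**What to change.** In the Analyses section, keep the odds ratio and add beside it, for the primary endpoint, the model-standardised coverage in each arm and the risk difference in percentage points with a cluster-adjusted 95% confidence interval, averaged over the random effects and covariates. State that if generalized estimating equations replace the mixed model, the same marginal risk difference will be reported from that fit, so that a fit failure changes the estimation method and not the target.

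The cost is a change of wording and one post-estimation step (delta method or cluster bootstrap). Sample size, data collection and trial conduct are unchanged.
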